## Abstract

**Background:**

Despite the growing prevalence of depression and anxiety among adolescents, fewer than half access appropriate mental health care. Single-session interventions (SSIs) for depression and anxiety offered in primary care are a promising approach to bridging the treatment gap.

**Objective:**

We aimed to implement a clinical workflow for primary care and behavioral health providers to refer patients aged 13 to 17 years with mild to moderate depression and anxiety symptoms to Project YES (Youth Empowerment and Support), an open-access SSI platform, in a large group medical practice with an integrated behavioral health department.

**Methods:**

Pediatric primary care and integrated behavioral health providers will be educated on the benefits of Project YES for adolescent anxiety and depression and trained in a workflow integrated within the electronic health record system, Epic, to refer patients during well-child visits and pediatric behavioral health visits. Patients with mild to moderate internalizing symptoms based on the 17-item Pediatric Symptom Checklist or youth Pediatric Symptom Checklist will be invited to try an SSI through Project YES. We will examine provider uptake and perceptions of acceptability, feasibility, and appropriateness over time.

**Results:**

The rollout will take place between November 2022 and May 2023, when outcomes will be evaluated. Data analysis and manuscript writing are anticipated to be completed during the summer of 2023.

**Conclusions:**

SSIs such as those available through Project YES have the potential to provide low-cost, evidence-based mental health treatment to adolescents with mild to moderate depression and anxiety. If deemed feasible and acceptable, providing SSIs in primary care settings could significantly improve access to mental health care without taxing pediatric primary care and behavioral health providers.

**International Registered Report Identifier (IRRID):**

DERR1-10.2196/45666

## Introduction

### Overview

Among adolescents, the incidence of depression and anxiety has increased significantly over the past decade. In 2019, 37% of adolescents (in the United States) experienced symptoms of sadness or hopelessness, while 21% received a diagnosis of major depressive disorder and 9% were diagnosed with an anxiety disorder [1]. Exacerbating the crisis in youth mental health, the COVID-19 pandemic led to unparalleled disruption in the day-to-day lives of youth and adolescents. School and social events were put on hold, and they observed the consequences of COVID-19 in their families and communities, resulting in a 2-fold increase in depression and anxiety [2].

Despite the rising prevalence of mental health concerns among adolescents, 75% of adolescents with mental health conditions do not receive appropriate care [2] due to a lack of access and acute shortages of qualified pediatric mental health clinicians [2]. Primary care providers are increasingly called upon to identify and intervene with mental health concerns [3], and it is therefore critical for pediatric primary care providers to have effective tools to offer to patients and their families to help manage symptoms. However, such resources are often not available to primary care providers, and patients often wait months before receiving care from licensed mental health professionals following a referral from primary care. Self-guided and web-based single-session interventions (SSIs) are an effective treatment for adolescents with mild to moderate mental health concerns [4] and may provide a stopgap for patients in need of more intensive care who are waiting to receive services. This paper presents the protocol for a novel clinical process for pediatric and integrated behavioral health care providers to refer adolescent patients to use the SSI platform Project YES (Youth Empowerment and Support) at a large group medical practice with an integrated behavioral health department.

### Access to Mental Health Care Among Adolescents

In 2021, the surgeon general declared a mental health emergency, prompting responses from multiple sectors to allocate resources to pediatric mental health care [5]. Yet, despite such calls, the population-level mental health of adolescents has worsened throughout the pandemic as growing patient needs are compounded by acute shortages of qualified providers [2,6]. While more than half of all adolescents with mental health concerns do not receive any treatment, even among those who are treated, most do not complete a full course of evidence-based treatment and rarely attend more than 3 to 4 sessions [7]. Beyond the issue of supply and demand, barriers to accessing and completing a clinically appropriate course of treatment for mental health concerns are many. Among adolescents, stigma, shame, and beliefs about who seeks mental health care may inhibit adolescents from accessing necessary interventions [8]. Confidentiality from parents is another important barrier and the Adolescent Health Care Barrier Survey revealed that nearly 40% of adolescents reported forgoing mental health services because they did not want their parents to know [9]. These barriers highlight the need for evidence-based tools which are both acceptable and directly accessible to youth presenting with mood- and anxiety-based symptoms.

SSIs are designed to be intentionally brief, flexible, and potent. Digital SSIs, which can be web-based and self-guided, are a sustainable and low-cost means of disseminating evidence-based treatments at scale [4,10]. SSIs do not rely on patient-provider ratios and can be offered to many patients by just a few providers in under 5 minutes. Their broad accessibility can reduce stigma around mental health concerns and help to normalize the use of appropriate care, whether a patient is going through a challenging time or working through a persistent mental health condition. Furthermore, SSIs can be disseminated in a variety of settings, such as schools and through social media [10,11], and adolescents can use SSIs with confidentiality from their parents. Despite the demonstrated efficacy of SSIs disseminated through social media, they are seldom made available in pediatric health care settings. As digital technologies are increasingly leveraged to close the gap in mental health care, SSIs may provide an additional resource for providers to deploy to adolescent patients.

### Evidence for SSIs

Given their demonstrated effectiveness and flexible nature, web-based SSIs allow youth to access mental health support when and where they need it. A growing body of evidence suggests that SSIs hold the potential to reduce a variety of mental health problems. In a meta-analysis of 50 randomized controlled trials targeting youth mental health issues, SSIs were effective (Hedges *g*=0.32) in improving several clinically relevant outcomes [12]. Notably, SSI effectiveness did not significantly differ between therapist-administered and self-administered interventions. In addition, shorter (<60-minute) interventions were found to be as effective as longer SSIs [12].

In a randomized controlled trial, a virtual, self-administered growth mindset intervention reduced depression symptoms in high-symptom youth 9 months after completion [13]. Other trials of digital SSIs teaching growth mindsets similarly demonstrated their potential to reduce depression symptoms [14-16]. In a diverse group of adolescents recruited from all 50 US states, 2 SSIs improved youth agency immediately postintervention and decreased anxiety, depression, hopelessness, and restrictive eating behaviors 3 months later [17]. Importantly, these SSIs appear to be similarly effective for youth of diverse racial-ethnic identities, gender identities, subjective family social status, and sexual orientations [18].

Web-based SSIs have been evaluated in a more naturalistic setting through an open-access web-based platform called Project YES [19]. Project YES allows adolescents (aged 11 to 17 years) to choose from 3 web-based interventions, each of which spans approximately 30 minutes and includes a core element of evidence-based treatment [10]. Youth may choose from Project Personality (which teaches that personality traits can change), Project CARE (which centers on the benefits of self-compassion), or the Action Brings Change (ABC) project (which encourages youth to engage in activities to improve their mood). Youth can complete as many interventions as they would like, as often as they choose to, and entirely free of charge. In a pilot trial, adolescents who completed an intervention through the Project YES platform experienced immediate improvements in hopelessness, self-hatred, perceived control, and agency. In addition, youth rated the interventions as acceptable, and 34.32% of youth who started an intervention completed it [10]. This surpassed completion rates for other digital interventions in naturalistic settings (1%-28%) [20].

Project YES has also been culturally adapted and translated into Spanish for youth living in San Antonio, Texas. Through a series of semistructured focus groups, San Antonio youth stakeholders shared their lived mental health experiences and co-designed the adapted interventions [21]. San Antonio youth who completed an intervention in English experienced immediate improvements in hopelessness, self-hatred, and perceived agency. Similarly, youth who completed a culturally adapted and translated intervention experienced immediate improvements in self-hatred [21]. The completion rate was 49.6%, and the interventions were rated as acceptable by youth [21].

Each SSI in Project YES includes shared core elements thought to underlie its effectiveness. Namely, the interventions (1) present youth with brain science to validate the concepts introduced in the activity, (2) empower youth by placing them in an “expert” role, (3) promote retention of the material with “saying is believing” exercises, and (4) include vignettes from peers and valued others [19]. Conceptually, the SSIs operate by shifting proximal beliefs or behaviors (eg, hopelessness, agency, expectancy that change is possible), which are thought to spark behavior change underlying a longer-term reduction of internalized symptoms [17,22]. SSIs are designed with a few key assumptions: (1) something good can come in 1 session, and 1 session may be the last; (2) change can, and is expected to, occur in the moment; (3) and individuals already have the inner capacity to alter their thoughts, emotions, and behaviors to create meaningful change [23]. Altogether, web-based SSIs, such as those in Project YES, are promising options for delivering brief, evidence-based mental health support with the potential to fill need-to-access gaps [24] for youth experiencing mental health problems.

Although SSIs disseminated through social media have been explored in other contexts, less is understood about how to optimize their implementation in primary care settings and integrate them into existing clinical workflows. Identifying best practices for integrating SSIs into current pediatric provider workflows may give providers an additional resource to recommend to their patients experiencing symptoms of anxiety or depression. To this end, the primary objective of this quality improvement pilot is to establish the feasibility and acceptability of delivering a SSI to adolescents with mild to moderate depression and anxiety in pediatric primary care and behavioral health.

## Methods

### Setting

Reliant Medical Group (RMG) is a multispecialty group medical practice in Massachusetts. With 19 clinics, RMG provides services to 240,000 patients per year, including 64,000 pediatric patients, 29% of whom have been diagnosed with a mental health condition. RMG has an integrated behavioral health department in which patients are triaged by a licensed mental health care provider from primary care to integrated behavioral health services within RMG or in the community. The pediatric behavioral health team has 13 providers, including psychologists, master’s level clinicians, nurse practitioners, and psychiatrists who handle prescribing needs. However, the integrated model only serves one-third of the patient population. In 2021, a total of 1910 pediatric patients who were not appropriate matches for the integrated care model were referred outside of RMG to receive services in the greater community. RMG also has a practice research network that includes a team of research scientists and coordination staff to oversee research studies and evaluate quality improvement initiatives. This protocol was developed by a multidisciplinary team including a research scientist, pediatrician, pediatric psychologist, and pediatric psychiatrist in collaboration with the Lab for Scalable Mental Health at Stony Brook University.

### Study Design

This paper describes a quality improvement pilot designed to evaluate the feasibility and acceptability of disseminating Project YES in primary and behavioral health care, as well as evaluate short-term changes in mental health outcomes among participants.

### Patient Screening

Figure 1 displays the clinical workflow for screening and referring patients to Project YES. First, as part of routine mental health screening during well-child visits, pediatric primary care and behavioral health providers or their medical assistants administer either the 17-item Pediatric Symptom Checklist (PSC-17) [25] or the Youth PSC-17 (Y-PSC-17) [25] to all patients aged between 13 and 17 years. When the total internalizing symptom score is elevated on either of these scales, follow-up screeners such as the Patient Health Questionnaire-9 (PHQ-9) [26] and the General Anxiety Disorder-7 (GAD-7) [27] are administered. Information from these screeners is used to determine whether patients meet criteria for a clinical diagnosis on the spectrum of depression or anxiety and whether routine follow-up is necessary. The PHQ-9 and GAD-7 screeners are also routinely administered as independent screening tools by behavioral health providers as part of the behavioral health visit. Providers will have the opportunity to refer patients to Project YES when the following criteria in Textbox 1 are met:

**Figure 1 figure1:**
[figure not shown]
Clinical workflow for referring patients to Project YES.

Inclusion and exclusion criteria.
**Inclusion criteria**
Patient is aged between 13 and 17 years.Patient meets at least one of the following criteria at the visit or in the preceding 3 months: (1) Patient Health Questionnaire-9 (PHQ-9) score >5; (2) Y-PSC-17 or PSC-17 internalizing score ≥5; (3) total Youth 17-item Pediatric Symptom Checklist (Y-PSC-17) or 17-item Pediatric Symptom Checklist (PSC-17) score ≥15; and (4) General Anxiety Disorder-7 (GAD-7) score ≥5.Comfortable speaking and reading in either English or Spanish.
**Exclusion criteria**
Active suicidal ideation (score ≥1 on question 9 of the PHQ-9, if completed).

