### Best Practice Alert

When a patient meets the eligibility criteria, a best practice alert (BPA), displayed in Figure 2, will be triggered in Epic, RMG’s electronic health records (EHR) system. The BPA pop-up screen provides instructions for referring a patient to Project YES, including a brief overview of Project YES, its potential benefits, and how to access it. If the patient indicates that they are interested, the provider can offer SSI in 1 of 2 ways:

Send the patient a QR code or a link to participate in the SSI through MyChart (the patient front-end of Epic). The MyChart message will include a link to Project YES at the Lab for Scalable Mental Health website and instructions for participating.Provide the patient with a QR code displayed in the BPA that patients may scan using their mobile device, allowing for the retrieval of Project YES for later use. The QR code is also included in the after-visit summary for later use. The QR code will direct patients to Project YES at the Lab for Scalable Mental Health website.

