### Patient Participation

Patients will receive an invitation to participate with a link to the SSI and instructions for participating through MyChart (Multimedia Appendix 1). The patient will click on the link in their MyChart messages that will take them to the Lab for Scalable Mental Health’s website. They will be asked to select the module they want to participate in and indicate that they are aged between 13 and 17 years and a patient at RMG in Massachusetts before beginning. The patient will not enter any potentially identifying information. By entering that they are an RMG patient, the Lab for Scalable Mental Health will be able to filter RMG’s data for the program evaluation. Before and after completing the module, the patient will be invited to complete a series of anonymous, optional questionnaires within Project YES’ Qualtrics interface. In the event a participant in Project YES experiences distress, the Project YES platform provides a “Need help now?” button on the main website and on each page of the platform that leads to [28]. The linked page provides immediately accessible crisis resources such as the Crisis Text Line, the National Suicide Prevention Lifeline, and a Hotline for LGBTQ+ Youth.

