### Strengths and Limitations

Offering patients SSIs in primary care and behavioral health settings is an efficient and cost-effective approach to narrowing the treatment-to-service gap in adolescent mental health care. Approaching this as an implementation project will allow us to understand the feasibility, acceptability, and appropriateness of SSI delivery in a pediatric primary care and integrated behavioral health setting and thus identify potential barriers and facilitators providers may face when offering Project YES to their patients. This information may be used to iteratively adapt the clinical workflow described to streamline the process for providers and patients alike, thus improving uptake. This protocol was developed in close collaboration with a pediatric clinical team and feedback from leadership to ensure that it is relevant, efficient, and can be easily grasped and deployed by providers. Further, making the SSIs accessible to patients with a wide range of symptoms may help reduce stigma around mental health care. Finally, adolescents who may otherwise forgo behavioral health services due to concerns about their confidentiality from their parents can use the SSIs privately without their parents being notified.

Nonetheless, there are several limitations to the study design. Participation is contingent on elevated scores on the screener questionnaires. However, patients who may not meet clinical criteria may also benefit from the SSIs, which can be effective for subclinical internalizing symptoms. To address this, future iterations of this project may explore expanding referrals to all adolescent patients, regardless of meeting screening criteria, or advertising the program on waiting room monitors and in other patient-facing materials. Additionally, this work is only being piloted at a single-group medical practice in Massachusetts and may not be generalizable to other populations. Furthermore, RMG has a predominantly White, English-speaking patient population. Although the intervention is available to Spanish-speaking patients, more work may be needed to understand its feasibility and acceptability in other clinical contexts and among diverse patient populations. Finally, without the use of a placebo-control group to control for potential effects of participating in an SSI in and of itself, the effectiveness data from this study may overestimate potential improvements in symptoms.

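### The only exclusion (PHQ-9 question 9) cannot operate for a primary care patient who qualifies with no PHQ-9 on file, and the text describes no prompt that tells the provider so

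*Protocol article*

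**What the plan says.** Four statements in the Methods of the protocol article bear on this point.

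- **Entry (Textbox 1, Inclusion criteria).** Any one of four screener results is enough: PHQ-9 above 5, internalizing score of at least 5, a total checklist score, or GAD-7 of at least 5. The total-score criterion stands alone, with no internalizing condition: "3) total Youth 17-item Pediatric Symptom Checklist (Y-PSC-17) or 17-item Pediatric Symptom Checklist (PSC-17) score ≥15".
- **Exclusion (Textbox 1, Exclusion criteria).** There is only one: "Active suicidal ideation (score ≥1 on question 9 of the PHQ-9, if completed").
- **Follow-up screening (Patient Screening).** All patients aged 13 to 17 get the PSC-17 or Y-PSC-17 at well-child visits. Further screeners depend on one part of that result: "When the total internalizing symptom score is elevated on either of these scales, follow-up screeners such as the Patient Health Questionnaire-9" and the GAD-7 are then given. The section describes the PHQ-9 as routine, whatever the checklist shows, only for behavioral health visits.
- **Alert (Best Practice Alert).** "When a patient meets the eligibility criteria, a best practice alert (BPA), displayed in Figure 2, will be triggered in Epic". On its contents: "The BPA pop-up screen provides instructions for referring a patient to Project YES, including a brief overview of Project YES, its potential benefits". Access to the platform is covered as well.

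**The concern.** The sponsor chose suicidal ideation as the single reason not to refer an otherwise eligible adolescent. That exclusion depends on an answer to PHQ-9 question 9. In primary care, a patient can qualify by a route on which the described workflow never asks for the PHQ-9. The exclusion then passes by default, and nothing in the text says that the provider is told it was not checked.

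The visit matters because it is the step at which the check can be made for a known patient. Within Project YES, "The patient will not enter any potentially identifying information", and adolescents "can use the SSIs privately without their parents being notified". A risk missed at the visit could not later be traced to a patient from the platform's data. At stake is a patient safety step. No estimate is at stake.

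**Working it through.** The article states no figure on this point, so there is none to reproduce. The check sets the entry criteria against the screening workflow for a primary care patient with no earlier PHQ-9 on file.

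| Entry route | Does the text ensure a PHQ-9? | Can the exclusion operate? |
|---|---|---|
| PHQ-9 above 5 | Yes, it is the qualifying test | Yes |
| Internalizing score at least 5 | No. Follow-up screeners are called for, but the PHQ-9 is named only as an example | Only if the PHQ-9 is the screener chosen |
| Total score at least 15, internalizing not elevated | No. The condition for follow-up screeners is not met | No |
| GAD-7 at least 5 alone | No. A GAD-7 result does not imply a PHQ-9 | No, if only the GAD-7 was done |

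The third row, step by step:

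1. Total score at least 15, internalizing score below 5: the inclusion rule is met by the total-score criterion alone.
2. The internalizing score is not elevated, so Patient Screening does not call for the PHQ-9.
3. Question 9 has not been completed, so the exclusion does not apply.
4. The eligibility criteria are therefore met and the alert fires.

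Textbox 1 itself treats this combination as possible. If every total of 15 or more came with an internalizing score of 5 or more, the total-score criterion would add no patient beyond the internalizing criterion.

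Two readings are assumed. First, the elevated internalizing score in Patient Screening is taken to be the subscale that Textbox 1 lists separately from the total. Second, elevated is taken to mean at least 5, the Textbox 1 cut-off, because Patient Screening gives none. If the total score was meant instead, the third row is largely closed, but the second and fourth rows are unchanged.

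At behavioral health visits the PHQ-9 is routine, so the gap lies essentially in primary care. A PHQ-9 already in the record would also supply question 9, but the text does not require one.

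The article gives neither the number of patients on each route nor a PHQ-9 completion rate. The frequency cannot be derived and none is assumed.

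**The case against.** The strongest objection is that the two places where an extra step would appear cannot be seen. Figure 1 is the referral workflow and Figure 2 is the alert screen, and neither was available. The description of the alert is also introduced as a partial list. This stands: the point can say only that the text states no check, and the fix has to be conditional on what Figure 2 shows.

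The second objection is that this is a choice and not a slip. The words *if completed* show that the authors foresaw patients without a PHQ-9 and kept them in. Strengths and Limitations also favours access across a wide range of symptoms. This stands too, and the qualifier is not itself an error. It does not settle whether the provider should know that the exclusion was not checked.

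Third, the alert only prompts a clinician who is with the patient and can record the patient as inappropriate (Table 1). Each page of the platform carries a crisis button (Patient Participation). The platform is open access, so withholding an alert would not prevent use. These points lower the stakes, but none of them is a question 9 check. The limits on tracing risk through anonymous data apply to every participant and are not special to these routes.

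Two stronger readings are tempting:

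- A reader might infer that the internalizing trigger is the cause of the gap. The table shows otherwise: GAD-7 entry and the non-binding choice of follow-up screener leave the same opening. What the routes share is a missing question 9 result.
- A reader might also infer that the total-score criterion contradicts the Abstract, which says "Patients with mild to moderate internalizing symptoms based on the 17-item Pediatric Symptom Checklist or youth Pediatric Symptom Checklist will be invited". The Abstract leaves out the PHQ-9 and GAD-7 routes as well, so it is a condensed summary and not a competing rule.

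**Conclusion.** The point holds, at minor severity. As the text is written, the only exclusion cannot operate for a primary care patient who meets an entry criterion with no PHQ-9 on file. Total-score-only entry is the clearest case, and two other routes share the opening.

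The conclusion rests on the printed text alone, on the two readings stated in the working, and on the possibility that Figure 2 already carries a prompt. The number of patients affected is unknown.

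A reader might infer that adolescents with suicidal ideation will be referred unnoticed, or that the evaluation is compromised. The article supports neither. It gives no rate of ideation on these routes, nothing in it says that the alert replaces clinical assessment, and the feasibility and acceptability results do not depend on this check.

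**What to change.** Unless the alert screen in Figure 2 already does so, add one conditional line to the alert. It should appear on any entry route whenever no question 9 result is on file: *PHQ-9 question 9 not on file: ask about suicidal ideation before offering Project YES.* Because the line depends only on the missing result, it covers all the open routes at once.

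It needs no new questionnaire and no new staff, and no patient loses the alert. The downside is a slightly longer pop-up and a brief extra question for some patients. The Results section already describes a one-site start to confirm that the Epic components work, and iterative review to identify adaptations, so the change fits the existing process.

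Extending the follow-up trigger in Patient Screening to a total score of at least 15 is optional. It would close only the total-score route, and even there only if the screener then given is the PHQ-9. It would also cost an extra screener for each such patient in primary care, a number the article does not give.
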